### Sample size

In a previous study [23] the DDS-scores were normally distributed with a standard deviation of 0.8. If the true difference between the experimental and control means is 0.4 [23], we will need to study 64 experimental subjects and 64 control subjects with a power of 0.8 and a Type I error of 0.05. In a recent local study in 10 health clinics, the intraclass correlation coefficient (ICC) for HbA1c was 0.011 [70]. For cluster randomised clinical trials the standard sample size calculation needs to be inflated by a factor: 1 + (n – 1) ρ, where n is 20 (the average cluster size) and ρ is 0.015 (the estimated ICC for this study) [71]. This inflation factor is 1.285. This gives a total sample size of 165. Since we anticipate a 20% drop-out rate, we will ask eligible patients for participation until at least 198 have signed informed consent.

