### Study setting - the clusters

Clusters are the public health clinics (HC) with more than 1000 T2DM patients in urban and suburban areas in the state of Negeri Sembilan, Malaysia. These clinics are the bigger public HCs with resident doctors and family medicine specialists (FMS) providing diabetes care in accordance to the Malaysian national clinical practice guideline [60]. Other inclusion criteria: the HCs have at least two nurses available to be trained for the intervention and the HC will/should not be participating in other similar studies. Out of 14 public HCs that fulfilled the above criteria and were invited to participate, 10 agreed.

These HCs are generally equipped with in-house facilities ranging from medical laboratory tests, plain X-rays to pharmacy. The public primary care service usually comprises of a multi-disciplinary team approach in patient care consisting of nutritionists or dieticians, pharmacists, physiotherapists, occupational therapists and paramedics who have undergone specialised training to provide services such as diabetes education. Patients in these HCs generally are managed by medical and health officers (M&HO) and supported by specialised nurses and dieticians/nutritionists. Nurses contribute in measuring clinical parameters during patients’ visits and give health education at the appointment day. Under the current health system, every patient diagnosed with T2DM will receive a green booklet which will be kept by the patient. This is accompanied by a bigger green medical record book (kept at the health clinics) that records all information pertaining to the care provided. Patients who have complications are referred to the hospitals either for admission or for shared care as outpatients with the hospitals’ specialists including endocrinologists or diabetologists.

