### Statistical analyses

Data will be entered and checked for accuracy by two separate person before analysis. The principal investigator has the overall responsibility for compilation, maintenance and management of the study database. The database is stored on a password-protected computer in a locked office. Analyses will be carried out by both an intention-to-treat approach and a per protocol analysis. Data will be checked for normality and multicollinearity, and if necessary transformed. Estimates will be obtained with PASW 22.0 (SPSS, Chicago, IL).

One-way analysis of variance (ANOVA) and *χ*
^2^ tests, as appropriate, will be conducted to test for baseline differences across the two treatment conditions and to examine differences in outcomes between dropouts and continuing participants. The difference between the groups will be analysed using a 3-level mixed model to account for clustering of measurements within patients and patients within general practices. The random part of the model will include a random intercept per practice and an unstructured correlation matrix for the correlation of measurements within patients. The fixed part of the model will include the variables time (categorical), treatment group, a group*time interaction and the baseline DDS-17 score; the difference in DDS-17 score at 6-month will be tested using a linear contrast. If necessary a multiple imputation technique will be used for missing data. A calculated 95% confidence interval and two-sided α of 0.05 will be used to test significance.

We will evaluate how baseline predictors are related to baseline DDS-17 score (cross-sectional analyses). Second, we examine how the baseline predictors are related to linear change in DDS-17 score over time (prospective analyses). Third, we will explore a set of time-varying covariates: how changes in a predictor over time are related to changes in DDS-17 score over time. Similar statistical modelling will be carried out on secondary outcome measures. Continuous outcome variables will be analysed using linear mixed models and binary outcome variables using generalized linear mixed models.

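### The 80% power corrects the variance for clustering but not the reference distribution for ten clinics; on 8 between-clinic degrees of freedom the unadjusted power is about 70%

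*Protocol article*

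**What the plan says.** The Sample size section takes the DDS-17 mean score as the outcome. It reports that "the DDS-scores were normally distributed with a standard deviation of 0.8" in an earlier study and continues: "If the true difference between the experimental and control means is 0.4", then "we will need to study 64 experimental subjects and 64 control subjects with a power of 0.8 and a Type I error of 0.05". The total of 128 is inflated by 1 + (n – 1)ρ, "where n is 20 (the average cluster size) and ρ is 0.015 (the estimated ICC for this study"). This gives a factor of 1.285, a total of 165 and, after an allowance for 20% drop-out, at least 198 to enrol. The only ICC reported from data is for another outcome: "the intraclass correlation coefficient (ICC) for HbA1c was 0.011".

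The clinics are the unit of randomisation (Aims of the trial). Of 14 eligible clinics that "were invited to participate, 10 agreed" (Study setting). These ten are randomised after stratification by size and area (Cluster randomisation).

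Under Statistical analyses, the 6-month difference in DDS-17 is a linear contrast from a mixed model adjusted for baseline DDS-17. "The random part of the model will include a random intercept per practice", and a "two-sided α of 0.05 will be used to test significance".

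**The concern.** Clustering has two consequences for a trial of this kind. Patients in the same clinic resemble one another, so the variance of the treatment contrast grows; the design effect deals with that. And the between-clinic variation has to be estimated from few clinics, so the test statistic has heavier tails than a normal variable; the design effect does not touch that. With several dozen clinics the second consequence is minor. With ten it is not.

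The plan handles only the first. Its power of 0.8 comes from a t test on 126 degrees of freedom, where ten clinics in two arms leave 10 − 2 = 8. If the trial ends with a non-significant difference, readers will weigh it against a stated 80% chance of detecting 0.4. If the real chance was nearer 70%, they would take the result as stronger evidence of no effect than it is.

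The figure is also sensitive to the ICC. The value used, 0.015, is the plan's own estimate, set above the 0.011 found for HbA1c. The article reports no ICC for DDS-17, a self-reported outcome that the trial tries to change through groups led by each clinic's own nurses.

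**Working it through.** **Inputs from the protocol article.** SD 0.8, difference 0.4, two-sided alpha 0.05, ICC 0.015, cluster size 20, 20% drop-out, 198 enrolled, 10 clinics. **Assumed:** five clinics per arm and equal clinic sizes.

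**1. The plan's own chain.** For a two-sample t test with 64 per arm, SE = 0.8 × √(2/64) = 0.1414 and the noncentrality is 0.4/0.1414 = 2.83. With 126 df (critical value 1.98), power is 80.1%. The design effect is 1 + 19 × 0.015 = 1.285, and 128 × 1.285 = 164.5, rounded to 165. The 198 equals 165 × 1.2. So 64, 1.285 and 165 all reproduce.

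**2. The plan's 165, with the reference distribution changed.** SE = 0.8 × √(2 × 1.285/82.5) = 0.1412; noncentrality 2.83.
- On 163 df: power 80.4%.
- On 8 df (critical value 2.31): power 70.0%.

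Only the degrees of freedom differ between these two lines.

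**3. The patients expected to complete.** 198 × 0.8 = 158.4, or 79.2 per arm and 15.84 per clinic. The design effect is 1 + 14.84 × 0.015 = 1.2226. SE = √(2 × 0.64 × 1.2226/79.2) = 0.1406; noncentrality 0.4/0.1406 = 2.85.
- On 8 df: power 70.4% (80.7% with patient-level df).
- 80% power on 8 df needs a noncentrality of 3.20, so the detectable difference is 3.20 × 0.1406 = 0.45.
- If all 198 were analysed, power on 8 df would be 77.7%.
- If the stratification factors used cluster-level df, power would be 68.6% on 7 df and 66.2% on 6 df.

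**4. Sensitivity to the ICC and to baseline adjustment** (158.4 completers, 8 df). Adjustment is taken to multiply the SD by √(1 − r²) and to leave the ICC unchanged. All values of r, and the ICCs 0.03 and 0.05, are assumptions.

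| ICC | Design effect | Unadjusted power | r = 0.3 | r = 0.4 | r = 0.5 |
|---|---|---|---|---|---|
| 0.015 | 1.223 | 70% | 74% | 78% | 82% |
| 0.03 | 1.445 | 63% | 67% | 71% | 75% |
| 0.05 | 1.742 | 55% | 59% | 63% | 68% |

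**5. Type I error if a normal reference were used.** In 200,000 simulated balanced trials (five clinics per arm, 16 analysed per clinic, REML random intercept), an uncorrected test rejected a true null in 5.3% of runs at ICC 0.015 and 7.2% at 0.05. At ICC 0.015 its power was about 79%. With Satterthwaite-type df, the rejection rate at ICC 0.015 was 3.9% and the power 70.5%.

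**The case against.** Four points can be made for the plan.

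*The planned contrast is adjusted for baseline, and 70% is for an unadjusted one.* This stands. With an assumed correlation of 0.5 and ICC 0.015 the adjusted power is 82%, so a reader who infers that the actual test must fall short of 80% goes further than the documents allow. But the Sample size section neither states a correlation nor relies on one, so the adjustment does not support the calculation as written. It would also not suffice at a somewhat higher ICC: r = 0.5 with ICC 0.03 gives 75%.

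*The article does not say that the test will be uncorrected.* This stands too. A reader might infer an inflated type I error from the silence on degrees of freedom. The article does not support that: the method is commonly left to the SAP, which is not shown, and even an uncorrected test would run at about 5.3% at the plan's ICC. The silence is not an error.

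*The ICC of 0.015 was not simply taken over from HbA1c.* Correct. The HbA1c value is 0.011, and 0.015 is a higher estimate made for this study. Nothing in the article shows 0.015 to be wrong. What can be said is that no DDS-17 value supports it.

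*The arithmetic is right.* It is, for the steps shown. The fault is a missing step: no allowance for few clusters.

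**Conclusion.** The point holds for the power statement. On the plan's own sample-size inputs, a test that uses the between-clinic degrees of freedom has about 70% power, not 80%, and the difference it can detect with 80% power is about 0.45, not 0.4. This rests on five equal clinics per arm, 20% drop-out, ICC 0.015 and no baseline adjustment. Unequal clinics or df spent on strata would lower it; baseline adjustment would raise it by an amount that the article does not let one determine. An uncorrected test comes close to the stated power (about 79%), and keeps close to the stated alpha only while the ICC is about as low as assumed. It should be corrected, but it does not threaten the design: the effect is on how the trial's sensitivity is described and on how a null result would be read.

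**What to change.** In the Sample size section, restate the power as about 70% (detectable difference about 0.45) for 10 clinics and 198 enrolled, on 8 between-clinic degrees of freedom. Add a short table over ICCs from 0.015 to 0.05, and say that 0.015 is the study's own estimate. If credit is taken for adjustment for baseline DDS-17, state the assumed correlation and show the power with and without it.

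In the analysis section, or in the SAP if it is not already there, say that the 6-month DDS-17 contrast is tested with small-sample degrees of freedom (Satterthwaite or Kenward-Roger). The restated power and the two-sided 0.05 level then refer to the same test.

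The cost is a less favourable published figure and one added line in the analysis text. No extra patients or clinics are required.

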**Methods:**

A cluster randomised controlled trial will be conducted in 10 public health clinics in Malaysia, all providing diabetes care according to national clinical practice guidelines. Patients’ inclusion criteria: Malay, ≥ 18 years with T2DM for at least 2 years, on regular follow-up with one of three biomarkers HbA1c, systolic blood pressure and LDL-cholesterol sub-optimally controlled, and with a mean 17-item Diabetes Distress Scale (DDS-17) score ≥ 3. The intervention consists of four sessions and one booster over a period of 4 months that provide information and skills to assist patients in having proper perceptions of their T2DM including an understanding of the treatment targets, understanding and managing their emotions and goal-setting. The comparator is an attention-control group with three meetings over a similar period. With an estimated intra-cluster correlation coefficient ρ of 0.015, a cluster size of 20 and 20% non-completion, the trial will need to enroll 198 patients. Primary outcome: the between groups difference in proportion of patients achieving a mean DDS-17 score < 3 (non-significant distress) at 6 months post-intervention. Secondary outcomes will be the differences in the above mentioned variables between groups.

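### The 20% drop-out allowance is multiplied on (165 × 1.20 = 198), not divided out (165 / 0.80 = 207), so 198 enrolled leaves about 158 completers against the plan's own 165

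*Protocol article*

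**What the plan says.** The protocol article builds the number in steps, all in the Sample size section.

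- **Unadjusted size.** The starting points are a previous study in which "the DDS-scores were normally distributed with a standard deviation of 0.8" and a target difference ("If the true difference between the experimental and control means is 0.4"). These lead to "64 experimental subjects and 64 control subjects with a power of 0.8 and a Type I error of 0.05".
- **Clustering.** The total is inflated by 1 + (n − 1)ρ, where "n is 20 (the average cluster size) and ρ is 0.015 (the estimated ICC for this study"). The factor is given as 1.285, and "This gives a total sample size of 165".
- **Drop-out.** "Since we anticipate a 20% drop-out rate, we will ask eligible patients for participation until at least 198 have signed informed consent".

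The Methods paragraph of the Abstract gives the same inputs (ICC 0.015, cluster size 20, 20% non-completion) and concludes that "the trial will need to enroll 198 patients". Neither place says that the 20% is measured relative to completers, and neither explains the step from 165 to 198.

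**The concern.** The plan presents 165 as the number needed before any loss and 198 as the number that protects it against 20% loss. The three figures 165, 20% and 198 cannot all hold. If one in five of those enrolled is lost, 198 does not leave 165.

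What is at stake is whether the enrolment figure delivers the analysable number that the same paragraph calls for. The 198 counts signed consents, and according to the Recruitment section eligibility is confirmed again at a later first meeting. Any exclusion at that point would draw on the same allowance.

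**Working it through.** **Inputs** (Sample size section unless noted): SD 0.8; difference 0.4; power 0.80; α 0.05, two-sided (Statistical analyses: "two-sided α of 0.05 will be used to test significance"); cluster size 20; ICC 0.015; drop-out 20%; ten clinics (Study setting).

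**Reproducing the plan's figures**

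1. Standardised difference: 0.4 / 0.8 = 0.5. The two-sample t-test needs 63.8 per arm, i.e. 64, as stated. (The normal approximation gives 63, so the plan's figure is the t-test one.)
2. Design effect: 1 + 19 × 0.015 = 1.285, as stated.
3. Total: 128 × 1.285 = 164.48, i.e. 165, as stated.
4. Enrolment: 165 × 1.20 = 198.0, as stated. The plan therefore multiplied by (1 + d).

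**Checking the drop-out step**

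- Completers from 198 at 20% loss: 198 × 0.80 = 158.4, about 158, which is 7 short of 165.
- Loss that 198 can bear: 1 − 165/198 = 16.7%.
- Enrolment that leaves 165: 165 / (1 − 0.20) = 206.25, i.e. 207. Check: 207 × 0.80 = 165.6.
- Gap in enrolment: 207 − 198 = 9 patients, just under one per clinic.

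**Effect on power** (two-sided t-test, standardised difference 0.5, effective n per arm = N / 2 / design effect)

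| Completers N | Design effect | Effective n per arm | Power |
|---|---|---|---|
| 165 | 1.285 (stated) | 64.2 | 80.3% |
| 158.4 | 1.285 (stated) | 61.6 | 78.6% |
| 158.4 | 1.223 (15.84 completers per clinic) | 64.8 | 80.6% |

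The last row uses 158.4 / 10 = 15.84 completers per clinic and the plan's own ICC: 1 + 14.84 × 0.015 = 1.2226. The requirement on that basis is 128 × 1.2226 = 156.5, i.e. 157 completers, which 158 meets.

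**The case against.** The strongest reply is that nothing is really lost. The cluster size of 20 corresponds to patients enrolled per clinic (198 / 10 = 19.8), not to those analysed. With completers per clinic, the design effect is about 1.22, about 157 completers suffice, and 198 enrolled with 20% loss still gives 80.6% power. This calculation is sound, and it removes any firm claim that the trial falls below its stated power. It does not remove the inconsistency, because the document does not argue this way: it fixes the factor at 1.285 and the total at 165 before it turns to drop-out.

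A second reply is that the planned analysis is not a completers-only t-test. The Statistical analyses section describes an intention-to-treat mixed model over repeated measurements with baseline DDS-17 as a covariate, and multiple imputation if needed. Baseline adjustment alone could close the gap. With the factor held at 1.285, 80% power needs 2 × 63.77 × 1.285 = 163.9 completers. Since 158.4 / 163.9 = 0.967, a baseline-to-follow-up correlation r with 1 − r² = 0.967, i.e. r of about 0.18, would be enough. The documents give no correlation, so this is an assumption, and the sample size section claims no such credit. The reply lessens the consequence but does not reconcile the three figures.

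Third, the Sample size section gives 198 as a minimum. A reader might take it as a fixed stopping number; the wording does not support that, since recruiting 207 is permitted. Even so, a minimum that misses its own target at the stated drop-out rate is wrongly derived.

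**Conclusion.** The point holds as an arithmetic error in a stated figure. Given 165 required and 20% drop-out, 198 is too low by 9 enrolled patients, or about 7 completers. It covers 16.7% loss, not 20%. This follows from the plan's own numbers and needs only the ordinary reading of a drop-out rate as a share of those enrolled.

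The consequence is small. With the stated factor of 1.285 the loss is under 2 points of power (80.3% to 78.6%, t-test). With the design effect taken on completers per clinic, power stays above the planned 80%. A reader might infer that the trial is underpowered, or that its power should be restated as 79%. The documents do not support either: that value depends on holding the design effect at an enrolled cluster size while counting only completers. Nor does the error touch the planned analysis or the interpretation of the result.

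**What to change.** Make 165, 20% and 198 agree, in both the Sample size section and the Abstract, by one of these routes:

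1. **Restate.** Keep 198 and say that it allows for 16.7% drop-out, or that about 158 completers are expected at 20%. This changes the text only.
2. **Correct the minimum.** Replace 198 with 207 (165 / 0.80). This costs nine more patients over ten clinics.
3. **Re-derive the clustering step.** Base the design effect on completers per clinic (about 15.8, factor about 1.22), and replace 1.285 and 165 with that factor and about 157. Dividing out 20% then gives 157 / 0.80 = 196.25, i.e. 197, which 198 covers. This needs no extra patients, but the cluster size of 20 must be changed in both places and the reasoning written down.

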### Statistical analyses

Data will be entered and checked for accuracy by two separate person before analysis. The principal investigator has the overall responsibility for compilation, maintenance and management of the study database. The database is stored on a password-protected computer in a locked office. Analyses will be carried out by both an intention-to-treat approach and a per protocol analysis. Data will be checked for normality and multicollinearity, and if necessary transformed. Estimates will be obtained with PASW 22.0 (SPSS, Chicago, IL).

One-way analysis of variance (ANOVA) and *χ*
^2^ tests, as appropriate, will be conducted to test for baseline differences across the two treatment conditions and to examine differences in outcomes between dropouts and continuing participants. The difference between the groups will be analysed using a 3-level mixed model to account for clustering of measurements within patients and patients within general practices. The random part of the model will include a random intercept per practice and an unstructured correlation matrix for the correlation of measurements within patients. The fixed part of the model will include the variables time (categorical), treatment group, a group*time interaction and the baseline DDS-17 score; the difference in DDS-17 score at 6-month will be tested using a linear contrast. If necessary a multiple imputation technique will be used for missing data. A calculated 95% confidence interval and two-sided α of 0.05 will be used to test significance.

We will evaluate how baseline predictors are related to baseline DDS-17 score (cross-sectional analyses). Second, we examine how the baseline predictors are related to linear change in DDS-17 score over time (prospective analyses). Third, we will explore a set of time-varying covariates: how changes in a predictor over time are related to changes in DDS-17 score over time. Similar statistical modelling will be carried out on secondary outcome measures. Continuous outcome variables will be analysed using linear mixed models and binary outcome variables using generalized linear mixed models.

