### Cluster randomisation

In assigning the HCs to the VEMOFIT group (VG) or attention-control groups (AG), randomisation will be carried out after stratification by cluster size and geographical areas of the 10 HCs. A member of the Data Management Services team at the University Medical Center, Utrecht will carry out the randomisation. Figure 2 shows the flow of HCs and participants through trial.

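### The primary mixed model leaves out the factors used to stratify clinic randomisation; if they relate to distress, its interval is somewhat too wide and its test conservative

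*Protocol article*

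**What the plan says.** In the protocol article, Cluster randomisation states that "randomisation will be carried out after stratification by cluster size and geographical areas of the 10 HCs".

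Statistical analyses then sets out the model term by term. Fixed effects: "The fixed part of the model will include the variables time (categorical), treatment group, a group*time interaction and the baseline DDS-17 score". Random effects: "The random part of the model will include a random intercept per practice and an unstructured correlation matrix" for the repeated measurements. The test: "the difference in DDS-17 score at 6-month will be tested using a linear contrast", with "A calculated 95% confidence interval and two-sided α of 0.05 will be used to test significance". Secondary outcomes get similar models.

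Neither cluster size nor area appears in the fixed or the random part, and no other section brings them in. Because the terms are listed one by one, this is a stated choice and not a detail left to an unseen analysis plan.

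**The concern.** Stratifying the allocation balances the arms on cluster size and area. Whatever those factors contribute to DDS-17 then largely cancels out of the treatment comparison, so the true spread of the estimate shrinks. A model without the factors does not see this. It still attributes differences between strata to the random clinic intercept, and that intercept feeds the standard error. The reported interval and p-value then describe an unstratified trial.

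With only ten clinics, the clinic-level error term weighs heavily in the test. At stake are precision that the design may already have bought, and agreement between analysis and allocation.

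**Working it through.** **Plan's own figures.** Sample size states that "the DDS-scores were normally distributed with a standard deviation of 0.8", then "If the true difference between the experimental and control means is 0.4", "we will need to study 64 experimental subjects and 64 control subjects with a power of 0.8 and a Type I error of 0.05". An exact t-test with 64 per arm gives power 0.801. The design effect is 1 + 19 × 0.015 = 1.285; 128 × 1.285 = 164.5, so 165; 165 × 1.2 = 198. All stated figures are reproduced. The calculation does not involve the strata.

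**True spread of the estimate.** Inputs: SD 0.8, ICC 0.015, five clinics per arm, and 20 × 0.8 = 16 completers per clinic.
- Clinic variance: 0.015 × 0.64 = 0.0096. Patient variance per clinic mean: 0.985 × 0.64 / 16 = 0.0394.
- Nothing explained by strata: √[(2/5)(0.0096 + 0.0394)] = 0.140.
- Half the clinic variance explained and balanced out: √[(2/5)(0.0048 + 0.0394)] = 0.133.
- At an assumed ICC of 0.05, the same steps give √[(2/5)(0.032 + 0.038)] = 0.167 and √[(2/5)(0.016 + 0.038)] = 0.147.

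**What the planned model reports.** Simulation of a random-intercept model (REML, clinic variance truncated at zero), Satterthwaite-type t reference, true difference 0.4 for power, 20,000–40,000 null runs and 15,000 power runs per setting. Strata of 4 + 6 clinics, one added term:

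| ICC | Clinic variance explained | Level without / with strata | Power without / with strata |
|---|---|---|---|
| 0.015 | 0% | 3.9% / – | 71% / 69% |
| 0.015 | 50% | 3.1% / 3.6% | 71% / 73% |
| 0.015 | 100% | 2.3% / 3.2% | 71% / 77% |
| 0.05 | 50% | 2.6% / 4.4% | 54% / 65% |
| 0.05 | 100% | 0.7% / 3.2% | 51% / 79% |

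With two binary main effects at ICC 0.015 and half explained, the level goes from 3.0% to 3.4% and power from 70.6% to 71.0%. Across these codings and repeat runs, half explained gives a level of 3.0–3.3% without and 3.4–3.9% with the factors at ICC 0.015. At ICC 0.05 it gives about 2.5% and 4.2–4.4%, with power 53–54% and 62–65%.

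**How much is due to the omission.** In the power runs at ICC 0.015 (4 + 6 strata), mean standard error over true SD is:
- no strata effect: 0.1444 / 0.1396 = 1.03;
- half explained, factors omitted: 0.1457 / 0.1333 = 1.09;
- half explained, factors included: 0.1405 / 0.1333 = 1.05.

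So part of the excess comes from truncating the clinic variance at zero, and adjustment does not remove it. A regression on clinic means, which has no truncation, isolates the omission. With two binary terms and half explained, its level is 3.6% unadjusted and 4.6% adjusted at ICC 0.015, with power 69.8% and 69.9%.

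**Cost if the factors are irrelevant.** One term takes clinic-level degrees of freedom from 8 to 7: power 70.6% to 68.8% at ICC 0.015 and 56.2% to 54.4% at 0.05. Two terms leave 6: in the clinic-mean regression, 70.4% to 65.7% and 55.9% to 51.8%.

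**Assumptions.** The article gives no strata layout, share explained or ICC for DDS-17. The simulations use one six-month measurement and do not model baseline adjustment.

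**The case against.** The strongest reply is that, with ten clinics, clinic-level degrees of freedom are scarce and leaving out weak covariates is a legitimate trade-off. At ICC 0.015 the return is small and depends on the coding. With two binary terms and strata of 3 + 3 + 2 + 2, power moved from 70.5% to 69.5% and the interval half-width from 0.320 to 0.322 when half the clinic variance was explained. With a quarter explained, power fell from 70.4% to 66.7% and the half-width rose from 0.318 to 0.330. Fitting four separate strata (2 + 2 + 2 + 4) took it from 70.5% to 68.4% with half explained. Strong strata effects are also not obvious: the clinics lie in one state, are all large and follow one guideline, patients are enrolled at DDS-17 of 3 or more, and baseline DDS-17 is already in the model.

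This stands as to size, and it argues for few terms. It does not remove the mismatch. The sponsor chose these factors for stratification, presumably because they might matter. The ICC of 0.015 is an estimate set beside a local value of 0.011 for HbA1c; no ICC for a distress score is given. If the true ICC is nearer 0.05, the gain clearly outweighs the cost once strata explain about half of the clinic variance.

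Three stronger readings are tempting, and the documents do not support them:
- That the test runs below 5% whenever the factors matter. This needs a small-sample t reference, which the article does not specify. With a normal reference, ICC 0.05–0.10 and strata explaining 10–25% of clinic variance, the unadjusted level was 5.4–7.5%, because ten clinics are too few for a z-test.
- That adding the factors restores 5%. In the planned type of model at ICC 0.015 it does not.
- That the omission biases the effect or inflates false positives. It does neither; it lowers the level relative to the adjusted model.

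**Conclusion.** The point holds as a modest mismatch between analysis and design. If cluster size or area is related to DDS-17, and a t reference is used, the stated model gives an interval somewhat too wide and a conservative test. At the planned ICC with half the clinic variance explained, the standard error is about 9–10% too large in total, only partly because of the omission. Adjustment moves the level by roughly half a point and power by between nothing and about 3 points in most codings. The benefit is clear only at a larger ICC or with strong strata effects.

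The conclusion rests on assumed values for the share explained, the strata layout and the ICC of 0.05. It concerns the continuous six-month contrast described in Statistical analyses. It is a cheap improvement and does not threaten the validity of a positive result.

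**What to change.** Add the stratification factors to the fixed part of the primary and secondary models:
- as main effects only, coded as at randomisation, with as few terms as that coding allows;
- with a small-sample degrees-of-freedom method named in the plan, such as Satterthwaite or Kenward-Roger;
- with the model without the factors reported as a sensitivity analysis.

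This takes a sentence or two, fixed before the data are analysed, and needs no new data. Each term costs one clinic-level degree of freedom. If the factors are unrelated to the outcome, the loss is about 1–2 points of power for one term or 3–5 points for two. Factors coded with more levels would cost more.
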